### Participant recruitment and eligibility criteria

Participants will be recruited through a village meeting called by the village elder. During this meeting, an ADRA Supervisor together with a designated health professional (HP-doctor or nurse) will provide information about the program. Following the information session, a call for volunteers who meet the eligibility criteria will be made. To be considered eligible to participate in the study the individuals will:be 18 years of age or older;live permanently in the village (for the duration of the program)have a waist circumference of ≥92 cm for men and ≥80 cm for women (as levels at and above these are indicative of risk of NCD) [25];be prepared to engage in the ‘Live More’ intervention and monthly post-program meetings (total duration of 6 months);be able to provide their own meals (because this will enable compliance with the program’s dietary recommendations).

An equal number of males and females will be recruited for the study. No payments will be requested of participants and the participants will not receive any financial remuneration for their involvement.

Individuals will be considered ineligible to participate in the study if they meet one or more of the following exclusion criteria:unstable angina;myocardial infarction within the previous 12 months;coronary by-pass surgery within the previous 12 months;other medical contraindications for dietary change or increased physical activity, as determined by the HP;chronic infectious disease/s, as participants illness may affect participation in the program;are a direct relative of the village chief (to reduce bias in recruiting).

All eligible participants will be explained the consent process, and informed that all personal information will be confidential and anonymous. They will then be asked to sign or make their mark on the consent form or give the appointed HP for the study verbal consent to sign on their behalf in the presence of a witness (in case of literacy constraints).

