**Methods/Design:**

This study is a 6-month cluster-randomised controlled trial of 288 adults (equal proportions of men and women aged 18 years and over) with waist circumference of ≥92 cm for men and ≥80 cm for women in four rural villages in each of Fiji, Vanuatu and Solomon Islands. Participants will permanently reside in their village and be able to prepare their own meals. Two villages will be randomised to the ‘Live More’ intervention (*n* = 24) or to control receiving only country specific Ministry of Health literature (*n* = 24). Intervention participants will meet three times a week in the first month, then once a week for the next two months and once a month for the last three months. Themes covered include: NCDs and their causes; and the benefits of positive lifestyle choices, positive psychology, stress management, forgiveness and self-worth, and how these influence long-term health habits. Outcome assessments at baseline, 30-days, 3-months and 6-months include body mass index, waist circumference, blood lipids, blood pressure and blood glucose. Secondary outcomes include changes in medication and substance use, diet, physical activity, emotional health and supportive relationships, collected by lifestyle questionnaire at the same time points.

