## Methods/Design

### Study design

The ’Live More’ program will be evaluated using a cluster randomised controlled trial. The study design is illustrated in Fig. 1. The 6-month intervention will be conducted in three Pacific Island countries: Solomon Islands, Vanuatu and Fiji. In each country there will be two intervention villages and two control, resulting in a total of six intervention villages and six control villages across the three countries. Assessments will be conducted at baseline, and repeated at 30 days, 3 months and 6 months post baseline. The design, conduct and reporting of this study will adhere to the Consolidated Standards of Reporting Trials (CONSORT) guidelines for group trials.

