### Power calculation

Data from CHIP interventions conducted in Australia and New Zealand [20] were used for the power analyses. Power calculations were conducted on all the biometrics to be measured in the present study, which indicated that of all the biometrics, detecting a significant change in triglycerides would require the greatest sample size. Using an estimated mean baseline triglyceride level of 1.15 mmol/L with a standard deviation of 0.33 mmol/L, to achieve a 5 % level of significance with 80 % power will require 87 participants in each of the three countries. Allowing for a 10 % loss to follow up at 6 months, in each country a total of 96 participants will be recruited, constituting two intervention villages each with 24 participants and two control villages each with 24 participants. In total, 288 participants from the three countries will be involved in the study: 144 intervention and 144 control.

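### Entry on waist circumference does not exclude current pregnancy or recent delivery, although waist and the other main measures are followed as outcomes for 6 months

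*Protocol article*

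**What the plan says.** The protocol article, under Participant recruitment and eligibility criteria, lists who may enter. A participant must "be 18 years of age or older", with no upper limit, and must "have a waist circumference of ≥92 cm for men and ≥80 cm for women". The stated reason for the cut-offs is that waists at or above them point to NCD risk. The same section adds: "An equal number of males and females will be recruited for the study".

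The exclusions are also itemised: unstable angina, "myocardial infarction within the previous 12 months;coronary by-pass surgery within the previous 12 months", chronic infectious disease, being a direct relative of the village chief, and "other medical contraindications for dietary change or increased physical activity, as determined by the HP". Pregnancy and recent delivery are not named there or anywhere else in the article.

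On outcomes, the abstract states: "Outcome assessments at baseline, 30-days, 3-months and 6-months include body mass index, waist circumference, blood lipids, blood pressure and blood glucose". Under Outcome measures, the medical history items are heart problems, blood pressure and glucose, cancer and breathing problems. Pregnancy status is not listed, at entry or later.

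**The concern.** A waist of 80 cm or more is meant to mark NCD risk. In a pregnant or newly delivered woman it need not do so, yet she meets the criterion as written. Her waist and weight over the next 6 months then follow gestation or recovery from delivery rather than lifestyle. A woman enrolled late in pregnancy would show a large fall in waist and BMI whichever arm her village is in. Lipids, glucose and blood pressure are exposed in the same way.

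Two features make this more than a matter of drafting. The entry variable is itself an outcome, so the condition that gets a woman in also drives her later change. And because pregnancy status is not among the listed data, the article gives no means of identifying the affected values afterwards.

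**Working it through.** **Inputs from the article**

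- Sample (Power calculation): "In total, 288 participants from the three countries will be involved in the study: 144 intervention and 144 control". This agrees with the design: 3 countries × 4 villages × 24 = 288, and 6 villages × 24 = 144 per arm.
- Women (eligibility section): 288 / 2 = 144, or about 72 per arm. If the balance is applied within villages, which the article does not state, that is 12 per village.
- Follow-up (Study design): "Assessments will be conducted at baseline, and repeated at 30 days, 3 months and 6 months post baseline".

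**Does any listed exclusion cover the gap?** The only candidate is the clause left to the health professional (HP). It asks whether diet change or more activity is contraindicated. That is a test of fitness to take part, not of whether waist, BMI or blood values can be interpreted. Two HPs could apply it differently to an uncomplicated pregnancy and both would be following the text.

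**Size.** The article gives no pregnancy rate, no pregnancy-related waist change and no SD of waist change. The following are assumptions: 2–6% of the women pregnant or newly delivered at some point in the trial; a waist change of 5–20 cm each; an SD of waist change of 5 cm in everyone else.

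1. Women affected: 144 × 0.02 = 2.9 and 144 × 0.06 = 8.6, so about 3 to 9.
2. One affected woman in a village of 24: 5/24 = 0.21 cm to 20/24 = 0.83 cm on the village mean.
3. Three more affected women in one arm than in the other, all changing in the same direction: 3 × 5/144 = 0.10 cm to 3 × 20/144 = 0.42 cm on the arm mean.
4. If both arms hold the same share, each arm mean moves by p × s, where p is half the rate among women (half the arm are women) and s is the waist change. This runs from 0.01 × 5 = 0.05 cm to 0.03 × 20 = 0.60 cm, and it cancels in the comparison if the changes are alike in both arms.
5. Added variance: SD = √(25 + p(1 − p)s²). Lowest corner: √(25 + 0.0099 × 25) = 5.02 cm. Highest corner: √(25 + 0.0291 × 400) = 6.05 cm.
6. Chance that the two arms' counts differ by three or more, treating 72 women per arm as independent: 13%, 28% and 37% at rates of 2%, 4% and 6% (difference of two binomial counts). Clustering by village is ignored here.

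**The case against.** Four objections carry weight.

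- **The HP clause may exclude some of these women.** The HP is a doctor or nurse and takes a medical history at entry. That narrows the gap, but the clause is discretionary and aimed at a different question, so it does not reliably close it.
- **Handling of pregnancies that begin after baseline usually belongs in the analysis plan.** That plan is not shown, so the absence of an analysis rule is not a fault in this document. The point therefore rests on the entry criteria, which the article fixes as itemised lists, and on the listed data.
- **The sizes are assumed.** Step 3 needs all three excess women to change in the same direction. Late-pregnancy entrants lose waist and women who conceive gain it, so the effects partly offset. The trial was sized on triglycerides as the measure needing most participants, and no effect on triglycerides is quantified here.
- **Dropping observed values after randomisation is open to challenge.** This stands. The main analysis should keep everyone.

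A reader might infer that the waist criterion actively selects pregnant women. The documents do not support that: the criterion admits them, and nothing shows that they would be over-represented among volunteers from villages chosen for visible overweight. A reader might also infer that the comparison between arms is biased. Allocation is random by village and pregnancy can occur in either arm, so no systematic imbalance has been shown.

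**Conclusion.** The omission is real and modest in size. Applied as written, the criteria admit women whose entry waist and later change need not reflect NCD risk, and the listed data would not identify them. The main effect is noise; on the assumed inputs, an SD of waist change of 5 cm becomes 5.02 to 6.05 cm. Bias arises only through uneven spread over the six villages per arm, and an excess of three women then moves an arm mean by about 0.10–0.42 cm. These sizes rest wholly on the assumed rates, changes and SD. The gap in the criteria does not depend on them. The sample size is not affected.

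**What to change.** - Add current pregnancy and recent delivery at baseline, with the interval after delivery stated, to the exclusion list. Give outcome validity as the reason. The HP asks about both in the medical assessment already planned at entry.
- Have the HP record pregnancy status at 30 days, 3 months and 6 months, so that affected values can be identified.
- Keep all randomised participants in the main analysis. Add a sensitivity analysis that leaves out anthropometric and blood values taken during or soon after a pregnancy, using the same interval as for entry. This can go in the analysis plan.

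The cost is one exclusion line, one extra question per visit and a slightly smaller pool of eligible women in each village.

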### Power calculation

Data from CHIP interventions conducted in Australia and New Zealand [20] were used for the power analyses. Power calculations were conducted on all the biometrics to be measured in the present study, which indicated that of all the biometrics, detecting a significant change in triglycerides would require the greatest sample size. Using an estimated mean baseline triglyceride level of 1.15 mmol/L with a standard deviation of 0.33 mmol/L, to achieve a 5 % level of significance with 80 % power will require 87 participants in each of the three countries. Allowing for a 10 % loss to follow up at 6 months, in each country a total of 96 participants will be recruited, constituting two intervention villages each with 24 participants and two control villages each with 24 participants. In total, 288 participants from the three countries will be involved in the study: 144 intervention and 144 control.

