### Village eligibility criteria and randomisation

A village will be eligible to participate in the study if there is:an expressed endorsement and positive commitment by the village chief/community leader;observable overweight in the community (estimation of at least 40 % as observed by the ADRA Supervisor);relatively low literacy rate/education level in the potential participants as indicated by the community leader;adequate interest by residents who meet the participant eligibility criteria (described below) to achieve the required cluster sample size (described below);willingness to participate in the study as either a treatment or control site.

Once eligible villages are identified, ensuring they are not in immediate proximity to each other to avoid cluster contamination, the villages in each country will be randomised to either intervention or control by a researcher not familiar with the geographic location or nature of the village. Figure 1 shows the sequence for allocation of sites to treatment and control conditions.

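### The claimed 80% power per country takes no account of village randomisation: 87 per country matches an unclustered calculation, and no between-arm difference is stated

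*Protocol article*

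**What the plan says.** Under Study design, the program "will be evaluated using a cluster randomised controlled trial", and "In each country there will be two intervention villages and two control". Under Village eligibility criteria and randomisation, "the villages in each country will be randomised to either intervention or control". The village is therefore the unit of allocation, with four villages per country and twelve in all.

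The Power calculation section sizes the trial on triglycerides, because "detecting a significant change in triglycerides would require the greatest sample size". It uses an "estimated mean baseline triglyceride level of 1.15 mmol/L with a standard deviation of 0.33 mmol/L", 5% significance and 80% power, and concludes that this "will require 87 participants in each of the three countries". After a 10% allowance for loss to follow-up the figure becomes 96 per country, "constituting two intervention villages each with 24 participants and two control villages each with 24 participants", and 288 overall.

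**The concern.** The section sets out its sizing chain from inputs to 87, then 96, then 288, and no step allows for people in the same village resembling one another. Nor does any step allow for the fact that a two-against-two comparison gives very little information on between-village variation. The target is described as a change, with no size and no mention of a difference between arms, although a controlled trial is judged on that difference.

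The number and size of the villages are fixed in this paragraph, so a later analysis plan could not make the 80% statement true. At stake is how country-level results are read. If 80% power per country is taken at face value, a non-significant result in one country looks like evidence against the program, when that comparison had little chance of showing an effect. The protocol intends its findings to guide delivery across the South Pacific.

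**Working it through.** **Inputs from the protocol.** SD 0.33 mmol/L; alpha 0.05 (sidedness not stated, two-sided assumed); power 80%; 87 per country before loss; two villages per arm per country, six per arm overall. Followed-up village size m = 87/4 = 21.75. **Assumed, because the protocol gives none:** ICC of 0.01, 0.02, 0.05 or 0.10.

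**Step 1: where 87 comes from.** No target difference is stated, so 87 cannot be derived directly. Unclustered t-test calculations give:

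- two arms, difference 0.20 (standardised 0.20/0.33 = 0.61): 43.7 per arm, 87.4 in total;
- one group, change 0.10 (standardised 0.10/0.33 = 0.30): 87.4 in total;
- two arms, difference 0.10: 172 per arm.

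Either of the first two, at a round difference, gives 87 with nothing left over for a design effect. The step to 96 is the loss allowance alone: 87 × 1.1 = 95.7, or 87/0.9 = 96.7.

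**Step 2: if 0.10 was meant.** With 43.5 per arm and no clustering, SE = 0.33 × √(2/43.5) = 0.0708. The noncentrality is 0.10/0.0708 = 1.41, and power is 29%.

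**Step 3: if 0.20 between arms was meant, per country.** Design effect DE = 1 + (21.75 − 1) × ICC; effective n = 87/DE; SE = √(2 × 0.33² × DE/(2 × 21.75)). Power comes from the noncentral t with noncentrality 0.20/SE. It is computed first with degrees of freedom (df) from the effective n, which corrects for the design effect only, then with the 4 − 2 = 2 df of a village-level comparison.

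| ICC | DE | Effective n | SE | Power, DE only | Power, 2 df |
|---|---|---|---|---|---|
| 0 | 1.00 | 87 | 0.071 | 80% | 36% |
| 0.01 | 1.21 | 72 | 0.078 | 72% | 31% |
| 0.02 | 1.42 | 61 | 0.084 | 65% | 28% |
| 0.05 | 2.04 | 43 | 0.101 | 49% | 22% |
| 0.10 | 3.08 | 28 | 0.124 | 34% | 16% |

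Larger villages would not generally repair this. With two villages per arm the effective n per arm cannot exceed 2/ICC, which is 40 at ICC 0.05 and so below the 43.5 needed.

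**Step 4: pooled over the twelve villages.** SE = √(2 × 0.33² × DE/(6 × 21.75)); stratified by country, df = 12 − 3 − 1 = 8. The difference detectable with 80% power is 3.20 × SE, where 3.20 is the noncentrality that gives 80% power on 8 df.

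| ICC | Pooled SE | Power for 0.20 | Power for 0.10 | Detectable difference (mmol/L) |
|---|---|---|---|---|
| 0.01 | 0.045 | 97% | 50% | 0.14 |
| 0.02 | 0.049 | 95% | 44% | 0.16 |
| 0.05 | 0.058 | 85% | 33% | 0.19 |
| 0.10 | 0.072 | 69% | 23% | 0.23 |

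These rows use 12 × 21.75 = 261 people followed up from the 288 recruited.

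**The case against.** Five points can be made for the plan.

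- **The protocol does not say that it ignored clustering.** With no target difference stated, an inflation hidden in 87 cannot be strictly excluded. This stands as a limit on certainty. Still, 87 equals the unclustered result at a round difference under two readings, and no clustering step appears anywhere.
- **An article condenses, so a missing ICC or target difference might sit in a fuller document.** This is fair as far as the omissions go. The finding rests on what is stated: 80% power in each country, from four villages.
- **The SD is quoted with the baseline mean, and adjusting for baseline could recover precision.** If baseline and follow-up correlated at 0.6 (an assumption), the residual SD would be 0.33 × √(1 − 0.36) = 0.264. Power for 0.20 on the design effect alone would then be about 89%, 83% and 68% at ICC 0.01, 0.02 and 0.05. With 2 df it would be 43%, 38% and 30%, and only 48% at ICC 0. Baseline adjustment therefore does not rescue the per-country claim.
- **The outcome analysis under Statistical methods is not said to be per country, and pooled power for 0.20 is good up to an ICC of 0.05.** This is correct, and it confines the criticism to the per-country statement. The Power calculation nevertheless words its claim per country.
- **The ICC range is the reviewer's.** True: the size of the shortfall depends on it. Its direction does not, for a 0.20 difference and an SD of 0.33.

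**Conclusion.** The point holds. The statement that 87 people per country give 80% power does not fit a trial that randomises two villages per arm in each country. For a between-arm difference of 0.20 mmol/L and SD 0.33, any ICC above zero takes per-country power below 80%. Over ICCs of 0.01 to 0.10 it is 72% down to 34% on the design effect alone, and 31% down to 16% once the 2 df are respected. If 0.10 mmol/L was the intended between-arm difference, per-country power is 29% before clustering is considered.

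That 87 came from an individual-level formula is a strong inference rather than a statement in the protocol. The ICC values, the two-sided test and the back-solved differences are assumptions. The conclusion does not extend to a pooled analysis: with 0.20 mmol/L as target, the twelve villages together keep at least 85% power up to an ICC of 0.05. For 0.10 mmol/L, pooled power is 50% or less throughout the range.

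**What to change.** Rewrite the Power calculation paragraph. Withdraw the claim of 80% power within each country, and restate power for the between-arm comparison pooled over the twelve villages and stratified by country. Give the target between-arm triglyceride difference, the SD and what it refers to, an ICC range with its source (for example 0.01 to 0.05), the village size after loss, and the 8 df. With 288 recruited and 261 followed up, the difference detectable at 80% power is about 0.14, 0.16 and 0.19 mmol/L at ICCs of 0.01, 0.02 and 0.05. Country-level comparisons should be described as not powered at 80%.

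The cost is one reworded paragraph and a less favourable stated power or detectable difference. No additional villages or participants are requested.

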### Statistical methods

The (biomedical) data will be analysed using IBM™ Statistics (version 21). Continuous data will be expressed as number, mean, standard deviation (SD). Categorical data will be summarized as counts and percentages. For each country, differences between participants in the intervention and control groups at baseline will be examined using Chi square for categorical variables and independent samples t-tests for continuous variables. The extent of changes (percent, and mean with 95 % confidence intervals (CI)) from baseline, one month, three months and six months will be assessed using Analysis of Variance (repeated measures). For all analyses, results are considered significant at *P* < 0.05.

The qualitative data obtained through the various participatory, qualitative techniques listed above, will first be checked for accuracy with some of the participants and then with program staff (facilitators and supervisor). For the analysis, focus group data from the first village will be broken down into parts and examined for emergent categories (themes or patterns) and sub-categories, then coded. These categories and sub-categories may at this stage start to show a theory. Coding of the second focus groups will be done with the first in mind. Subsequent focus group discussion in the other two countries will also be coded with the emerging theory in mind.

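### The 80 % power stated for each country is not available from two villages per arm; power should be computed and stated for the pooled 12-village comparison

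*Protocol article*

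**What the plan says.** All references are to the protocol article.

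- Study design: the programme "program will be evaluated using a cluster randomised controlled trial". The layout is: "In each country there will be two intervention villages and two control, resulting in a total of six intervention villages and six control villages".
- Village eligibility criteria and randomisation: "the villages in each country will be randomised to either intervention or control by a researcher not familiar with the geographic location". Allocation is thus by village, within country.
- Power calculation: triglycerides are the outcome needing the largest sample, with a baseline mean of 1.15 and SD of 0.33 mmol/L. The target is "to achieve a 5 % level of significance with 80 % power", and this "will require 87 participants in each of the three countries". After a 10 % allowance for loss, "in each country a total of 96 participants will be recruited, constituting two intervention villages each with 24 participants and two control villages". The overall 288 is the sum of the three countries. No effect size, ICC or power for the combined trial is given.
- Statistical methods: the sentence that opens "For each country, differences between participants in the intervention and control groups" goes on to limit itself to baseline, using participant-level tests. Outcomes are assessed by repeated-measures analysis of variance at P < 0.05. The text does not say whether this is by country or pooled, and it names no village term.

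**The concern.** The only power figure in the article belongs to a comparison inside one country. There, four villages are randomised, and the programme effect has to be told apart from ordinary differences between one pair of villages and another. The 80 % can be read as true only if some 87 people count as independently randomised.

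Two things are at stake. The sponsor and readers may believe that each country can deliver its own significant answer. And the comparison that could carry a conclusion, all 12 villages together, has no stated power, so nobody can judge whether 288 people in 12 villages is enough.

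**Working it through.** **1. The article's own figures.** 87 × 1.1 = 95.7, which rounds to 96 (87/0.9 = 96.7 would round to 97; the difference is trivial). 4 villages × 24 = 96 and 3 × 96 = 288 are exact. The 87 itself cannot be reproduced, because no effect size is given.

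**2. Back-solving the effect (assumption: two-sided 5 %, 80 % power, SD 0.33).** The normal multiplier is 1.96 + 0.84 = 2.80.
- 87 as the total of two arms: 0.33 × 2.80 × √(4/87) = 0.198 mmol/L (17 % of 1.15).
- 87 per arm: 0.33 × 2.80 × √(2/87) = 0.140 mmol/L.
- 87 as a single group measured for change, SD 0.33: 0.33 × 2.80 / √87 = 0.099 mmol/L.

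The first reading fits the recruitment plan best, since 87 is inflated to 96 for both arms together.

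**3. Randomisation within one country.** Ways to choose 2 of 4 villages: C(4,2) = 6. The smallest two-sided p is 2/6 = 0.33. This needs no assumption about effect, SD or ICC.

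**4. Randomisation over the trial, stratified by country.** 6³ = 216 allocations, so the smallest two-sided p is 2/216 = 0.009.

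**5. t-test on village means.** With k villages per arm and m = 87/4 = 21.75 people per village at follow-up,

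SE = 0.33 × √[(2/k) × (ICC + (1 − ICC)/m)].

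- One country: k = 2, df = 4 − 2 = 2, critical t = 4.30.
- Pooled, country as stratum: k = 6, df = 12 − 3 − 1 = 8, critical t = 2.31.

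Example, one country, ICC 0: SE = 0.33 × √(1/21.75) = 0.0708 and 0.198/0.0708 = 2.80. A non-central t with 2 df and non-centrality 2.80 exceeds 4.30 with probability 35 %. Example, pooled, ICC 0.05: SE = 0.0583 and 0.198/0.0583 = 3.40, giving 84 %.

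The ICC values are assumed. Power in %:

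| Difference (mmol/L) | Comparison | ICC 0 | 0.01 | 0.05 | 0.10 |
|---|---|---|---|---|---|
| 0.198 | one country, 2 df | 35 | 31 | 21 | 16 |
| 0.198 | pooled, 8 df | 99 | 97 | 84 | 68 |
| 0.140 | pooled, 8 df | 85 | 78 | 56 | 41 |
| 0.099 | pooled, 8 df | 57 | 49 | 32 | 23 |

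Rounding 0.198 up to 0.20 moves the pooled figures at ICC 0.05 and 0.10 to 85 % and 69 %.

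**6. Where the lost power goes.** At ICC 0 the non-centrality of 2.80 equals the normal multiplier in step 2. So the fall from 80 % to 35 % comes wholly from having 2 degrees of freedom, before any clustering is assumed.

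**7. If village is ignored instead.** The true error of a nominal 5 % participant-level test is about 2 × [1 − Φ(1.96/√DE)], with DE = 1 + 20.75 × ICC. At ICC 0.01, 0.05 and 0.10, DE is 1.21, 2.04 and 3.08, and the error is about 7 %, 17 % and 26 %.

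**The case against.** The strongest reply is that the article never says conclusions on the outcomes will be drawn country by country. The per-country wording in Statistical methods governs baseline comparisons only. The Abstract and Study design describe one trial of 288 adults, with "resulting in a total of six intervention villages and six control villages across the three countries". Which analysis is primary, and whether country is a stratum, are matters an article may leave to a fuller document. All of this stands. A reader might infer from the sizing that three separate significance claims are planned, but the document does not support that. The error lies in the stated power.

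Second, a reader might conclude that no valid inference is possible within a country. That goes too far. A 2-df t-test on village means is valid under normality, and a large enough true effect could reach significance. What it lacks is useful power at the differences that 87 implies. The bar is absolute only for a randomisation test.

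Third, a reader might conclude that the trial is well powered once pooled. The document cannot show this, since it gives neither effect size nor ICC, and the table falls below 80 % under several plausible inputs.

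Finally, pooling alone does not respect the design. A repeated-measures analysis of variance with no village term, run on all 288 people, would still ignore the clustering.

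**Conclusion.** The point holds as an error in the stated power. With a randomisation test, P < 0.05 cannot be reached in a single country (minimum 0.33). With a village-level t-test, power is at most about 35 % against the claimed 80 %, and 31 % and 21 % at ICC 0.01 and 0.05.

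The randomisation result rests on the two-against-two layout alone. The t-test figures rest on a two-sided test, the stated SD of 0.33 mmol/L, 87 as the two-arm total (hence 0.198 mmol/L) and assumed ICCs. The other two readings of 87 imply smaller differences and so still lower within-country power.

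The pooled comparison can reach significance, but whether it has 80 % power is open. It does at 0.198 mmol/L and an ICC of 0.05. It does not at an ICC of 0.10, nor at 0.14 mmol/L once the ICC is 0.01 or more.

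**What to change.** 1. Replace the per-country statement in Power calculation with a power computed for the 12-village comparison, stratified by country, with village as the unit of analysis or a random effect and small-sample degrees of freedom (8 for the village-level test). State the effect size, the ICC with its source, and whether the test is two-sided.
2. Name that comparison as primary, and write the village and country terms into the outcome analysis in Statistical methods.
3. Report country-specific effects as descriptive estimates with confidence intervals, with an arm-by-country interaction and no significance test inside a country.

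No villages or participants are added by this wording. The cost is a stated power that may be less favourable than 80 %, and no per-country significance tests. If the computed figure is too low, the sponsor will know it before data are seen and can decide whether 12 villages suffice.
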